### **Study Design:**

This prospective, multicenter, randomized, open-label, parallel-group clinical trial will be performed at 20 hospitals across Sichuan in China. However, in practice, 15 sites fulfilled the study protocol and conducted the study.

Study participants will be randomized in a 1:1 ratio to a morning (6–10 am) or a bedtime (6–10 pm) administration group. Initially, each participant will receive one tablet of OA (20/5 mg) daily for 4 weeks and will be then followed up at 4-week intervals for a total of 12 weeks. The OA dosage will be adjusted according to the results of ABPM and OBPM during follow-up. Controlled BP is defined as a 24-h mean BP <130/80 mmHg, daytime mean BP <135/85 mmHg, nighttime mean BP <120/70 mmHg, and OBPM <140/90 mmHg. The OA dosage will be increased to 1.5 tablets/day in patients who are found to have masked or sustained uncontrolled hypertension at the initial follow-up visit. If BP remains uncontrolled after a further 4 weeks, the OA dosage can be increased further to 2 tablets/day. All participants are instructed to discontinue their preexisting antihypertensive medications for at least 2 weeks before starting the trial intervention. Adherence with medication will be recorded at each follow-up visit. Concomitant use of other antihypertensive drugs other than OA will be prohibited during this study.

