The medical officer assigned to each study participant is alerted to remind the participant to attend all interventions and assessments in an effort to minimize the dropout rate. Participants and their caregivers also have direct access to a hotline during office hours if they have any concerns or problems. All original research data are entered into the electronic data capture system, namely, the Red Shine Chronic Disease Management System developed by the Hypertension Center at West China

Hospital (<http://47.108.235.3:3003/#/login>). All study-related information is stored securely in the system and all information concerning individual study participants is stored in locked filing cabinets in areas with limited access. A training session on the study protocol was provided before initiation of the study at each participating site to ensure that the quality of this clinical trial is satisfactory. On-site monitoring at the beginning, middle, and the end of the study is performed by assigned clinical researchers to ensure complete compliance with the study protocol. A project specialist has been assigned to this trial for data monitoring, examination, and cleaning. This specialist will perform the interim analyses, the frequency of which will be decided by the specialist in consultation with the principal investigator. The specialist will advise the principal investigator of the interim findings if necessary. After data cleaning is completed, the data managers and statisticians will conduct a final review of unresolved data issues, discuss the division of datasets together according to the statistical analysis plan, and examine any reports of serious adverse events. A statistical analysis is to be conducted halfway through and at the end of the trial. The subjects will be discontinued from follow-up if individual participants report any serious adverse effects during the intervention or a significant deterioration in their mental or physical state.

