#### **Statistical Method:**

The study population is divided into a morning administration group and a bedtime administration group. Quantitative variables will be summarized as the mean  $\pm$  SD or as the median [interquartile range (IQR)] depending on the type of the original data.

Qualitative variables will be presented as the absolute and relative frequency. Quantitative variables will be compared between the two study groups using the t-test or Mann-Whitney U test and qualitative variables using the chi-squared test or Fisher's exact test.

All analyses will be based on the intention-to-treat (ITT) and the per-protocol (PP) populations. The primary objective of the study will be analyzed using an analysis of covariance (ANCOVA) model with appropriate baseline adjustments. The ANCOVA model will also be used to evaluate the other secondary objectives. Mean differences or odds ratios will be determined across groups along with their 95% confidence intervals. All statistical analyses will be performed using SPSS version 26.0 (IBM Corp., Armonk, NY, USA). The significance level will be set to 5% for all statistical tests.

The process for handling missing data is generally divided into the deletion of cases with missing data and imputation of missing data. The commonly used methods include mean imputation, last observation carried forward, and multiple imputation. We will deal with the missing data depending on the circumstances under the guidance of the Department of Clinical Research Management at West China Hospital.

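### One specialist both cleans the data and runs the interim analyses, and no masking is stated for diary-time queries, failed recordings or per-protocol membership in this open-label trial

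*Combined protocol and SAP*

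**What the plan says.** All references are to the combined protocol and SAP.

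- **Collection of medical data and quality control, roles.** Monitoring, examination and cleaning go to one person, who also has the interim looks: "A project specialist has been assigned to this trial for data monitoring, examination, and cleaning. This specialist will perform the interim analyses". That person settles how often the looks take place, together with the principal investigator. Results can travel further: "The specialist will advise the principal investigator of the interim findings if necessary". The section also schedules a statistical analysis halfway through and at the end.
- **Same section, later step.** A different group then acts: "After data cleaning is completed, the data managers and statisticians will conduct a final review of unresolved data issues". That group is also to "discuss the division of datasets together according to the statistical analysis plan".
- **Same section, recordings.** A valid ambulatory recording must span more than 20 h, with at least 20 day and 10 night readings. Night is the interval from falling asleep to waking, and participants note on a diary card when they go to bed and wake.
- **Statistical Method.** "All analyses will be based on the intention-to-treat (ITT) and the per-protocol (PP) populations". No membership rule is written for either set, and the missing-data method is left to circumstances.
- **Study Design.** The study is a "randomized, open-label, parallel-group clinical trial". The document states no masking of the specialist, data managers or statisticians, and no database lock.

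**The concern.** The overlap of roles is written into the plan; it is not merely inferred from silence. Once the first interim analysis has been run, the person still raising and closing data queries may know how the arms compare.

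Three kinds of decision remain open to judgement:

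1. **Diary times.** Moving a sleep or wake time changes which readings form the nocturnal mean, and can decide whether a recording reaches 10 night readings. The diary asks for bedtime while the definition uses falling asleep, so some queries are to be expected. The plan does not say how such times are corrected.
2. **Recordings that fail the validity rule.** The plan does not say what happens to them. With the missing-data method also open, this can affect the ITT analysis as well as the PP analysis.
3. **PP membership.** The later group is sent to the statistical analysis plan for a rule, but the Statistical Method section contains none.

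At stake is whether a reader can exclude result-aware decisions as an explanation for a small difference, and whether the PP analysis says anything independent of the ITT analysis.

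**Working it through.** **The plan's own figure.** Inputs from Sample Size Consideration: difference 3 mmHg, SD 12 mmHg, two-sided 5%, power 85%, 20% dropout. Allocation is 1:1 (Study Design).

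- Normal formula: n = 2 × (1.960 + 1.036)² × 12² / 3² = 287.3, so 288 per arm. The t-based solution is 288.3, so 289, as stated.
- Dropout: 288/0.8 = 360, as stated (289/0.8 = 361.25, so 362).
- With 289 per arm, SE = 12 × √(2/289) = 0.998 mmHg, and the smallest significant difference is 1.96 × 0.998 = 1.96 mmHg.

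The sample size reproduces and is not in question. It supplies the scale.

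**Size of the opportunity.** The documents do not say how many patients would be judgement calls, so this share is an assumption, shown over a range.

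- No true difference, SD 12, 288 analysed per arm.
- Judgement calls: k = 14 per arm (5% of 288) or k = 29 (10%).
- Half of the calls end in exclusion. An uninfluenced call is a coin toss. An influenced call keeps the patient only if the outcome favours one particular arm.
- Share of calls influenced: f = 0.5 or 1.

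The mean of the favourable half of a normal distribution with SD 12 is 12 × √(2/π) = 9.57 mmHg from the centre. The number left per arm is N = 288 − k/2. Both arms move in opposite directions, so:

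shift = 2 × f × (k/2) × 9.57 / N, and SE = 12 × √(2/N).

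With r = shift/SE, the rejection rate is P(Z > 1.96 − r) + P(Z < −1.96 − r).

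| k per arm | f | N | Shift (mmHg) | SE | r | Rejection rate |
|---|---|---|---|---|---|---|
| 14 | 0.5 | 281 | 0.24 | 1.012 | 0.236 | 0.042 + 0.014 = 5.6% |
| 14 | 1 | 281 | 0.48 | 1.012 | 0.471 | 0.068 + 0.008 = 7.6% |
| 29 | 0.5 | 273.5 | 0.51 | 1.026 | 0.495 | 0.071 + 0.007 = 7.9% |
| 29 | 1 | 273.5 | 1.02 | 1.026 | 0.989 | 0.166 + 0.002 = 16.8% |

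Simulation of the same model with a t-test (40,000 trials per setting) gave 5.6%, 7.4%, 7.8% and 16.7% in the same order. With pure coin tosses it gave 5.1% and 4.9%, so exclusion alone does no harm; only exclusion that follows the result does. Runs with 8,000 to 40,000 trials gave 4.9–5.7%, 7.1–7.8%, 7.9–8.2% and 15.0–17%.

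**A harsher model, for contrast.** Suppose 360 per arm, and only patients lying 12 to 18 mmHg on the unfavourable side are removed. Then shift = 2 × k × d/(360 − k). With k = 7 (2%) this is 2 × 7 × 12/353 = 0.48 to 2 × 7 × 18/353 = 0.71 mmHg, and the rejection rate is 8.2–12.4%. This needs deliberate picking of extreme patients, which nothing in the text suggests. It is not used for the conclusion.

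**The case against.** Much can be said for the plan, and several stronger readings fail.

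- **A reader might infer that which recordings count is open.** It is not. The validity rule is numeric and was fixed in advance. Discretion lies around it: diary times and the treatment of failures.
- **A reader might infer that the specialist chooses the analysis sets.** The text gives that step to data managers and statisticians, with the statistical analysis plan as their reference. Dividing sets after cleaning is ordinary practice. The weakness is doing so with no masking stated and no written PP rule.
- **A reader might infer that the specialist necessarily knows the between-arm result, or that decisions were steered by it.** The plan does not say whether the interim analyses compare arms, and silence on masking does not show that arm and outcome were in view.
- **A reader might infer that the ITT contrast can be moved by choosing members.** ITT has a settled meaning: all randomised participants, as assigned. Membership discretion concerns PP. The ITT result is exposed only through diary corrections and through failed or missing recordings. Writing out the two definitions would, by itself, only supply missing detail.
- **The error rates rest on assumed shares.** The top figures require every call, in both arms, to go the same way. With 5% judgement calls and half influenced, the effect is negligible: 0.24 mmHg against a planned 3. The calculation also uses an unadjusted comparison, not the planned ANCOVA.

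All of this stands, and it limits the point. It does not remove the stated assignment of cleaning and interim analysis to one person, or the lack of any masking statement for the decisions that remain.

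**Conclusion.** The point holds as a modest weakness of conduct. One specialist cleans the data and performs the interim analyses. Final review and set division follow, and no masking is stated in an open-label trial. The exposed decisions are diary sleep and wake times, recordings that fail the validity rule, and PP membership. The risk from interim knowledge arises only if the interim analysis compares arms.

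Assuming 5–10% of patients are judgement calls, the shift is about 0.25–0.5 mmHg (type I error about 5–8%) if half are influenced, and about 0.5–1.0 mmHg (about 7–17%) if all are. These figures describe an opportunity. The documents give no evidence that it was used. The number of interim looks and the control of the 5% level are separate matters.

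**What to change.** Change Collection of medical data and quality control in two places.

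1. **Mask and lock the decisions.** Cleaning, diary-time corrections, recording-validity decisions, the final review of unresolved issues and PP membership are done on listings with the arm removed. Dosing time appears only as a yes/no flag for whether it fell in the assigned window. Week-12 BP is also hidden for set-membership decisions. All these decisions are locked before arm is merged. ITT stays all randomised participants as assigned and is not open to discussion.
2. **Separate the roles.** Any between-arm interim tabulation is run by one of the statisticians already named in the section. That person takes no part in cleaning, final review or set division, and does not pass arm-level results to those who do. Barring that person from cleaning alone would not be enough, because the statisticians also sit in the final review.

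The cost is a short change of wording and a data export without the arm column, using existing staff. The sample size is unaffected. There are two downsides: the cleaner cannot use arm to spot wrong dosing-time entries, which the flag largely covers, and one statistician is kept out of the data review.

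Study Duration reports follow-up until April 2024. If these steps are already done, the sponsor can instead state who had access to arm and interim results, and whether diary, validity and set decisions were made masked.

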However, managing nocturnal BP is challenging in practice. Antihypertensive chronotherapy may provide a new direction for effective management of nocturnal BP. A recently published multicenter, prospective, randomized controlled study from Spain (known as Hygia Chronotherapy Trial) found that taking antihypertensive medication before bedtime significantly reduced the risk of cardiovascular death, myocardial infarction, and major cardiovascular composite events (including coronary revascularization, heart failure, or stroke) in hypertensive patients. However, a two-center randomized, crossover, prospective clinical study performed in London and Thessaloniki suggested that the timing of antihypertensive drug delivery (morning vs. nighttime) did not affect 24-h BP, daytime BP, or nocturnal BP levels in hypertensive patients. Furthermore, the clinical evidence for antihypertensive chronotherapy comes mostly from populations on a single antihypertensive agent in Europe or the USA or from populations with cardiovascular disease. High heterogeneity, including in intervention methods, evaluation indicators, and study populations, between these studies has been noted. Moreover, a systematic review of 21 studies that compared antihypertensive medication taken in the morning with that taken at bedtime indicated that both dosing strategies showed no statistical

67 difference in 24-h mean BP reduction values. Thus, the clinical benefit of taking  
68 antihypertensive drugs before bedtime remains controversial.

69 Therefore, we planed to initiate this prospective, randomized, open-label,  
70 parallel-group clinical study to compare the effects of morning and bedtime  
71 administration on nocturnal BP reduction and recovery of circadian rhythm in patients  
72 with essential hypertension. The results of this trial are expected to provide useful  
73 guidance for optimizing BP control, particularly in Chinese patients with  
74 hypertension.

75 **Primary Objective:**

76 The decrease in average nocturnal SBP between baseline and after 12 weeks of the  
77 intervention.

78 **Secondary Objective:**

79 24-h ambulatory BP measurements

80 1. Reductions in 24-h, daytime and morning average SBP and diastolic BP (DBP) at  
81 weeks 4 and 12.

82 2. Average 24-h, daytime, nocturnal SBP and DBP control rates at weeks 4 and 12.

83 3. Changes of proportion of non-dipper, and changes in BP load.

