**Collection of medical data and quality control:**

This research is initiated by [name] at the Hypertension Center, West China Hospital, Sichuan University. Trained physicians, nurses, and clinical research coordinators (CRCs) are required to keep medical records and collect data in accordance with the study protocol.

Baseline data on demographic characteristics, height, and body weight will be collected, and blood biochemistry tests will be performed. Office BP will be measured using calibrated electronic sphygmomanometers (HBP-9020, Omron Corp., Kyoto, Japan) according to the guidelines for the management of hypertension (However, due to budget constraints, we decided to switch to the Omron HBP-1100-E (Omron Healthcare Co., Ltd, Kyoto, Japan) before the trial commenced). To obtain accurate BP data, all participants are requested to rest for 5 min before the measurement. SBP and DBP are obtained three times on the right arm in a sitting position, with the average of the last two values calculated as mean office BP. ABPM

readings are obtained from the non-dominant arm at baseline and weeks 4 and 12 using a TM2430 BP monitor (A&D Inc., Tokyo, Japan). During monitoring, BP is measured at 20 min intervals throughout the day (usually from 6 am to 10 pm) and then at 30 min intervals at night (usually from 10 pm to 6 am). Valid recordings will span >20 h, including at least 20 during the day and 10 during the night. A diary card is issued to each participant so that they can record their schedule in detail, including the times they go to bed and wake up. The mean 24-h BP was calculated as the average of all successful values. Nighttime BP was defined as the mean BP recorded between falling asleep and waking up. Daytime BP was defined as the mean value of all other readings. Morning BP was defined as the average BP within 2 hours after waking up. Circadian rhythms were categorized according to the extent of nocturnal fall in BP: extreme dipper (>20% fall); dipper (10-20% fall); non-dipper (0 to <10% fall); and reverse dipper (<0% fall). The nocturnal fall in BP was calculated as (Daytime BP-Nighttime BP)/Daytime BP\*100%. BP load was defined as the percentage of readings above the normal value during the daytime, nighttime, or 24-h period.

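### The plan ends follow-up after a serious adverse effect or marked deterioration, which leaves some randomised participants without the week-12 endpoint and undermines the ITT analysis

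*Combined protocol and SAP*

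**What the plan says.** All references are to the combined protocol and SAP.

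- **Collection of medical data and quality control, the rule.** "The subjects will be discontinued from follow-up if individual participants report any serious adverse effects during the intervention". The wording is mandatory, and what ends is follow-up. The sentence then gives a second trigger: "or a significant deterioration in their mental or physical state". Deterioration has no threshold and no named assessor.
- **Same section, retention.** Staff are to remind participants to attend all assessments "in an effort to minimize the dropout rate".
- **Same section, schedule.** Ambulatory BP "readings are obtained from the non-dominant arm at baseline and weeks 4 and 12".
- **Same section, safety.** Serious adverse event reports are examined at the final data review. Nothing is said about following an event to its outcome or recording later events.
- **Primary Objective.** "The decrease in average nocturnal SBP between baseline and after 12 weeks of the" study treatment.
- **Statistical Method, populations.** "All analyses will be based on the intention-to-treat (ITT) and the per-protocol (PP) populations". Neither population is defined.
- **Statistical Method, missing data.** After naming case deletion and imputation, the text says "The commonly used methods include mean imputation, last observation carried forward, and multiple imputation". It does not choose among them but leaves the matter open: "We will deal with the missing data depending on the circumstances under the guidance" from a hospital department. No method is fixed.
- **Study Design.** The trial is open-label. Uncontrolled BP leads to a dose increase with continued follow-up. Antihypertensives other than the study drug are prohibited.

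**The concern.** Stopping a study drug and stopping observation are different events, and the documents do not separate them. An ITT analysis of week-12 nocturnal SBP needs the week-12 value from every randomised participant as far as it can be obtained. This rule chooses in advance not to obtain it for some of them.

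Both triggers occur after randomisation, and one rests on participant report in an open-label trial. If the participants removed differ between arms in number or in BP course, the comparison of those who remain is no longer fully protected by randomisation. Adjusting for baseline in the ANCOVA does not restore values that depend on what happened later. With no missing-data method fixed, nothing downstream is committed to dealing with this.

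The rule also ends observation just when a serious event has been reported, so the plan does not provide for learning how that event resolved.

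**Working it through.** **1. Which values are lost.** With ambulatory BP at baseline, week 4 and week 12 only:

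- removed before week 4: no post-baseline ambulatory value;
- removed between weeks 4 and 12: a week-4 value, but no primary endpoint value.

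**2. The plan's own sample size.** Inputs from Sample Size Consideration: difference 3 mmHg, SD 12 mmHg, two-sided alpha 0.05, power 85%.

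- Normal approximation: n = 2 × (1.960 + 1.036)² × 12² / 3² = 287.3, so 288 per arm. The exact t calculation gives 289, the stated figure.
- Dropout of 20%: 288 / 0.8 = 360, the stated figure (289 / 0.8 = 361.25, so 362).

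The stated figures reproduce to within two patients. The point does not rest on a wrong number.

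**3. Precision.** Unadjusted standard error at 289 per arm: 12 × √(2/289) = 1.0 mmHg.

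**4. Power.** 360 × 0.8 = 288 evaluable per arm gives 85.1%. If removals fall within the 20% allowance, nothing is lost. If they come on top of it (assumed):

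| Extra loss | Evaluable per arm | Power |
|---|---|---|
| 1 point | 284 | 84.6% |
| 2 points | 281 | 84.2% |
| 5 points | 270 | 82.8% |

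Power is therefore not the main issue.

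**5. Shift in a completers' analysis.** The documents give no event rates, so all rates and gaps here are assumptions. Let p be the proportion removed in an arm and D the mean SBP change that the removed would have shown minus that of the retained. The full-arm mean is the retained mean plus p × D, so the completers' mean is off by −p × D. The arm difference is off by −(p₁D₁ − p₂D₂).

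- *Same gap, unequal rates* (size of shift = imbalance × gap):

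| Imbalance | Gap 5 mmHg | Gap 10 mmHg | Gap 20 mmHg |
|---|---|---|---|
| 2 points | 0.1 | 0.2 | 0.4 |
| 5 points | 0.25 | 0.5 | 1.0 |

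- *Equal rates, unequal gaps:* 2% removed with gaps differing by 5 mmHg gives 0.02 × 5 = 0.1 mmHg; 10% with gaps differing by 10 mmHg gives 0.10 × 10 = 1.0 mmHg.
- *Equal rates and equal gaps:* zero.

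The range 0.1 to 1.0 mmHg is 3% to 33% of the 3 mmHg target. On 360 per arm, an imbalance of 2 points is about 7 participants and one of 5 points is 18, so the upper end needs a large imbalance.

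**6. If last observation carried forward were chosen.** For removals before week 4 it would carry baseline forward, a change of 0. If those participants would otherwise have shown the 14.7 mmHg reduction cited in Sample Size Consideration, each point of imbalance shifts the difference by 0.01 × 14.7 = 0.15 mmHg, and 5 points by 0.7 mmHg.

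**The case against.** Several counter-arguments have force.

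- **Who is removed.** A reader might infer that the rule takes out participants whose BP is badly controlled and leaves a set who are doing well. The documents do not support that. Study Design keeps uncontrolled participants in follow-up with a dose increase, and the need for intensified treatment is itself a listed outcome. The link between the triggers and nocturnal SBP is plausible but not documented.
- **ITT.** A reader might say that the rule contradicts ITT. That is too strong: removed participants can still be analysed in their assigned arm by imputation, and the plan expects missing data. What stands is that the analysis would lean on imputed values where observed ones might have been had, with no method chosen. The open missing-data plan is a defect in its own right, and part of the harm belongs to it.
- **Safety.** A reader might infer that a between-arm safety comparison is being censored. The objectives contain no such comparison, and the triggering report is still examined. What stands is narrower: the event's outcome and later events are not provided for.
- **Size.** Both arms start on the same drug and dose, treatment lasts 12 weeks, and several serious cardiac conditions and haemorrhagic stroke are excluded, so events may be rare. This stands, and limits the point.
- **Wording.** The sentence may be loose phrasing for stopping treatment only. Even so, sites would have to act on the text as written, and no other text says that assessments continue.

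**Conclusion.** The point holds as one of data completeness and of what the ITT analysis can estimate. Followed as written, the plan withholds the week-12 primary endpoint from every participant removed before that visit and makes no provision for event follow-up. That reading rests on the text alone and is firm.

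That the missingness biases the comparison is an inference, held with less confidence. The illustrative 0.1 to 1.0 mmHg rests entirely on assumed rates and gaps. It is zero when these are equal in both arms, and no more than about one standard error at the top of the range. If events are rare, the effect on the primary result is probably modest. The correction is worth making because it is cheap and because data not collected cannot be recovered by analysis.

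**What to change.** Reconcile the Collection of medical data and quality control section with the Statistical Method section:

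1. Separate the end of data collection from any decision about study medication. That decision is for the clinicians and is not specified here.
2. State that participants covered by the rule stay in scheduled assessments, including week-12 ambulatory monitoring, and in follow-up of the event, where they consent and are able.
3. Record drug discontinuation separately from study withdrawal, each with date and reason.
4. State how BP values obtained after discontinuation, or after other antihypertensives have been given, enter the ITT analysis. This is needed because Study Design prohibits those drugs during the study, while participants who remain under observation may receive them.
5. Define the ITT set and fix the method for week-12 values that are still missing.

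Study Duration reports that follow-up lasted until April 2024. Where visits are over, an amendment cannot recover data. Instead, report removals under this rule by arm, timing and reason, and add a sensitivity analysis for their missing week-12 values.

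The cost is a few additional assessments at visits already scheduled, event follow-up for the participants concerned, and a short analysis rule.
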